** *Payment mechanism* **	Providers paid per block of 100 deliveries (20% in advance)	Payment to woman at the time of discharge from hospital after delivery
** *Quantum of payment* **	A flat amount of INR 288000($5760) is paid to the obstetrician per 100 women (regardless of delivery type)	INR1400 ($28) to rural mothers on discharge (INR1000 to urban mothers).
** *Expected effect* **	Provides access to EmOC care – which is available more widely	Increase institutional delivery, hence access to EmOC
** *Support for Emergency transport* **	Centralized 108 ambulance system	Decentralized Janani Express model

This protocol describes the proposed comprehensive evaluation of two respective programs in Gujarat and Madhya Pradesh. The evaluation, called the MATIND project is a four year project supported under the EU FP7 framework. The proposal aims to study (i) trends in program uptake since inception(ii)the influence of the program on institutional delivery rates, maternal and neonatal outcomes, (iii) explore service providers’ experiences,(iv) emergency transportation systems for obstetric referrals,(v) characteristics of the facilities participating in the programs, (vi) quality of care administered, (vii)experiences of the beneficiaries and non-beneficiaries, (viii) the role of community health workers and (ix) the cost effectiveness of the programs.

The program evaluation will be conducted at three different levels of the health system with specific objectives at each level: (i) the provincial (policy) level which includes secondary data from governments and other important stakeholders at the provincial level, (ii) the district level (sub-provincial) which focuses on health facilities (iii) and the community level, in villages (sub-district), which includes mothers and local health workers.

The objectives at each level of the study are listed below and summarized in Table 2:

1. Provincial (policy) level:

(i) Program Trends: To describe trends in program uptake for each program since inception and to study district level time series of program uptake data from 2004 to 2011. Further to examine the extent to which changes in the proportion of institutional deliveries have influenced maternal and neonatal outcomes over that period of time.

(ii)Private Sector Participation: To describe trends in private sector (health facilities) participation in each of the programs over time. Also, to study the characteristics of private sector participant facilities.

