Data on delivery outcomes for women admitted in the facility will also be collected over a five day period at each facility that had more than 10 deliveries in a month. A research assistant, assigned to the facility, will administer a short questionnaire to mothers who deliver within the defined time frame. Basic socio-demographic characteristics, pregnancy and delivery details, and indication for referral if appropriate will be elicited. More specific details of the same delivery will be obtained from the nurse in the labor ward. These will include type of delivery, presence of known pregnancy or delivery related complications, maternal and neonatal outcomes. This will provide information on the proportion of these events among program mothers. In the case of CY, it will allow a comparison with non-program mothers who deliver at the same time in the program hospitals. This study will provide a cross sectional snap shot of outcomes for program mothers. The proportion of program mothers who have complications, who undergo instrumental delivery, referred, who have adverse neonatal outcomes will be reported as will the number of maternal deaths during this period.

The Hulton et al. Quality of Care framework will be used to assess the quality of care (objective vi) from both the provision of care (facility perspective) and the experience of care (user perspective) [14]. Observations of normal deliveries, case record and register reviews, competency rating of service care provider, mother’s experience and the referral process will all be used to ascertain the quality of care being administered to obstetric patients.

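### The five-day facility survey is announced for women admitted but enrols only women who deliver there, so women referred out undelivered go unrecorded at the sending facility, which mainly affects the CY comparison

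*Protocol article*

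**What the plan says.** Under Data collection methods, Facility Level, the survey is introduced by its population: "Data on delivery outcomes for women admitted in the facility will also be collected over a five day period". It runs "at each facility that had more than 10 deliveries in a month". The assigned research assistant is then to "administer a short questionnaire to mothers who deliver within the defined time frame". The second source is tied to the same event: "More specific details of the same delivery will be obtained from the nurse in the labor ward". No step in that paragraph covers a woman who is admitted and leaves undelivered.

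The planned output is stated next: "The proportion of program mothers who have complications, who undergo instrumental delivery, referred, who have adverse neonatal outcomes will be reported", and "as will the number of maternal deaths during this period". For CY, program mothers are to be compared with non-program mothers delivering in the same program hospitals over the same days.

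Two other places bear on the point. Table 1 (Background) describes the CY payment: "A flat amount of INR 288000($5760) is paid to the obstetrician per 100 women (regardless of delivery type". The Community level text defines a CY participant as a below-poverty-line or tribal mother who delivers in a CY-approved facility, and a JSY participant as a woman who delivers in any public facility. Those definitions are written for the community survey; the facility survey gives none of its own.

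**The concern.** The announced population and the enrolment rule differ, and the women who fall between them are not a random subset. Transfer before delivery may well follow from a complication. If so, enrolling on delivery in the facility removes complicated cases from both numerator and denominator at the facility that sends them away, and a facility that refers out more will look safer.

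The CY comparison is the most exposed. It is made inside program hospitals, so a woman transferred to a non-CY hospital leaves it even if she is surveyed where she delivers. If the community-survey definition is carried over, she also stops being a program mother. The flat CY payment gives a possible reason for program women to be referred out more often than other women in the same hospital. In that case the two arms of the comparison would be thinned unequally.

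**Working it through.** The document gives no event rate, referral rate or sample size for this survey, so there is no stated figure to reproduce. What can be checked is which women each rule captures and how the bias behaves under assumed rates.

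**1. Who is recorded where**

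| Woman | At sending facility | At receiving facility |
|---|---|---|
| Admitted, delivers there | enrolled | not applicable |
| Admitted, referred out, delivers at a surveyed facility | not enrolled | enrolled if she delivers in its window |
| Admitted, referred out, delivers outside the district or at a low-volume facility | not enrolled | not enrolled |

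Under the community definitions, a JSY woman moved between public facilities stays a program mother. A JSY woman moved to a private facility, or a CY woman moved to a non-CY facility, does not.

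**2. Complication proportion, allowing for recapture**

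All inputs are assumptions:
- r = share of admitted program women referred out undelivered
- cd = complication rate in women delivered in place, set at 10%
- cr = complication rate in women referred out, set at 50%
- q = share recaptured as program mothers at a surveyed receiving facility

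True = (1−r)·cd + r·cr

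Reported = [(1−r)·cd + r·q·cr] / [(1−r) + r·q]

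For r = 10%: true = 0.90×0.10 + 0.10×0.50 = 14.0%. Reported is 0.09/0.90 = 10.0% at q = 0, (0.09+0.025)/(0.90+0.05) = 12.1% at q = 0.5, and 14.0% at q = 1.

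| r | True | q = 0 | q = 0.5 | q = 1 |
|---|---|---|---|---|
| 5% | 12.0% | 10.0% | 11.0% | 12.0% |
| 10% | 14.0% | 10.0% | 12.1% | 14.0% |
| 20% | 18.0% | 10.0% | 14.4% | 18.0% |

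The q = 0 column is what a sending facility sees of its own admissions, whatever happens elsewhere. If cr = cd there is no bias.

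**3. An illustration in which only complicated cases are sent out and none is recaptured**

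Let p be the true complication rate and s the share of complicated cases sent out. Observed = p(1−s) / [p(1−s) + (1−p)].

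- p = 15%: s = 30% gives 0.105/0.955 = 11.0%; s = 50% gives 0.075/0.925 = 8.1%
- p = 10%: 7.2% and 5.3%
- p = 20%: 14.9% and 11.1%

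This sets q = 0, so it is an upper bound on the bias under its assumed rates. With half of those women recaptured, p = 15% reads as 0.1275/0.9775 = 13.0% (s = 30%) or 0.1125/0.9625 = 11.7% (s = 50%).

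**4. The CY comparison**

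Suppose both groups in a program hospital truly have 14.0% complications. Program women follow the r = 10% row above with transfers going to non-CY hospitals, and no non-program woman is referred out. The survey then shows 10.0% against 14.0%, a difference of 4 percentage points created by enrolment alone. If both groups were referred out alike, both would read low and no difference would be created.

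**5. Outward referral**

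Among women enrolled at the sending facility, the proportion referred out before delivery is 0 whatever r is. With r = 10% and half recaptured, the pooled data show 0.05/0.95 = 5.3%, and show it as women referred in.

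**The case against.** The strongest reply is recapture. The survey covers every facility above the volume threshold, drawn from a verified list of public and private facilities in the study districts. A woman transferred before delivery will often be enrolled where she delivers. Windows need not coincide: with windows of equal length and steady flow, referred-in deliveries at surveyed hospitals represent the transfers those hospitals receive, in expectation. This stands, and it means a general understatement for program mothers in both schemes, which a reader might infer, is not supported. Pooled JSY figures lose women only where the destination is unsurveyed or private. Recapture does not restore the sending facility's own figures, nor the CY comparison when the destination is a non-CY hospital.

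Other stronger readings also fail:

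- **Referral proportion.** A reader might infer that the promised proportion referred is near zero by construction. But objective vi and the referral interviews speak of women referred in, and the word may mean that here too. On that reading the proportion is not understated by this mechanism; outward referral is simply not measured.
- **Deaths.** The death count is not tied to questionnaire respondents, and the plan maps referral pathways of maternal deaths. Undercounting after transfer is possible but not shown.
- **Public–private and between-program contrasts.** The sentence that plans these concerns facility characteristics, not this outcome survey. The main impact comparison uses the community sample, which covers mothers regardless of place of delivery.
- **CY referral behaviour.** Nothing in the document says that CY obstetricians refer complicated cases out. The flat payment makes it possible, no more.

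It may also be said that an admission log is operational detail for the full protocol. That would answer a mere silence. Here the article states an enrolment rule, and the rule is narrower than the population it announces.

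**Conclusion.** The point holds in a limited form. The enrolment rule omits women admitted and referred out undelivered. Outward referral before delivery is therefore unmeasured at the sending facility. Complications are likely understated there and in the CY same-hospital comparison, provided that women referred out have more complications than those delivered in place. For the comparison to be distorted, referral out must also differ between CY and non-program women. Both conditions are plausible; neither is documented. Whether a transferred CY woman leaves the program group altogether depends on whether the community-survey definition is applied.

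The size cannot be fixed from the document. Under the assumed rates the shortfall at a sending facility is 2 to 8 percentage points (10.0% against 12.0% to 18.0%), and in pooled figures it falls to zero at full recapture. The flaw affects a cross-sectional snapshot and one comparison, not the evaluation as a whole, but it should be corrected because selection is likely related to the outcome and the remedy is simple.

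**What to change.** Define the study population as all women admitted for delivery during the five-day window. Have the assigned research assistant log each admission from the admission register or the labor ward nurse, with program status fixed at first admission. Record referral out undelivered, with reason and destination, or death as an outcome. Use admissions as the denominator for complications and for referral out. Report referred-in and referred-out women separately, and keep facility deliveries as a secondary denominator so that the results can be set beside delivery-based figures.

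The cost is about one log line per admission, kept by staff already assigned to the facility. The drawback is less outcome detail for women referred out, whose complications would be known only up to the point of transfer unless they are also enrolled where they deliver.

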(vii) Program beneficiaries and non-beneficiaries: To study and compare beneficiaries and eligible non-beneficiaries of the program in the community in terms of: socio-demographic characteristics, utilization of antenatal services, birth attendance, delivery outcome, birth weight, receipt of post natal care, immunization of the child and costs of care incurred. Reasons for participation/non participation and choice of place of delivery will be explored. Predictors of non-participation will also be studied.

(viii) Equity in access to facilities (geographic): To estimate the influence of distance to facilities on place of delivery in comparison to other determinants of delivery service use.

(ix) Role of community health workers in program uptake: To study the role played by the ASHA (accredited social health activist) and the traditional birth attendants (TBA) in the antenatal, delivery and postnatal periods of program mothers. Also to explore among ASHAs their motives for participation and long term professional aspirations within the NRHM. The dynamic between various community level workers, the TBA, the ASHA and the female health worker will be explored. Concerns on the potential duplication of roles between the latter two will be explored among policy makers.

**Table 2 T2:** Summary of objectives and proposed methods at the implementation level

**Study level**	**Objectives**	**Proposed methods**
Provincial (Policy)	To study program utilization trends	Secondary data analysis - complete times series, Document reviews, Key person interviews with policy makers, program managers and private sector representatives, Stakeholder discussions
	To ascertain the influence of changes in ANC service utilization and institutional deliveries on maternal and neonatal outcomes	
	To study trends in private sector participation	
	Explore the motivations for participation/non participation with the private sector in CY program	
	To understand the exclusion of the private sector in the JSY program	
	Explore experience of private provider in JSY	
	Comparison of emergency care transportation systems	
	Cost effectiveness of the programs and the emergency transportation models	
District (Facility)	List and classify all facilities performing deliveries according to their EmOC functionality	Facility Survey, Observations of normal deliveries, Register and case record review, Case vignettes to study provider competence, In depth exit interviews with mothers

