For the observations, content analysis will be used to conceptualize and classify events, behaviors and actions to obtain a rich understanding of quality of care and explanation of how women experience care at facilities [16]. Basic descriptive statistics will be calculated for key indicators from the record and register review. With regard to provider competence, descriptive analysis will identify competence areas that require strengthening. The data will be analyzed using inferential statistics to compare scores between levels of facilities and qualification and experience of providers. The data from exit interviews will be analyzed to describe use of evidence based practices by level of facility. Qualitative data derived from the in-depth interviews with mothers will be analyzed using the thematic Framework approach [17]. The obstetric referrals, indications for referral and details of referral-transport, costs, distance, and time will be described by the level of facility using mean, standard deviation and tests of significance. The referral pathways of the maternal deaths will be mapped on GIS and buffer analyzed. The buffer analysis will be used to study referring facility locations with regard to transfer time to CEmOC facilities.

3. Community level (mothers in the study villages):

At the community level we will collect primary data from recently delivered mothers to compare outcomes between eligible beneficiaries and non-beneficiaries (objective vii) for each of the programs. A cross-sectional study will be conducted with women residing in the selected study villages who delivered in the last year. JSY program participation is defined as an institutional delivery in any public health facility. Program non participation is defined as a home or private facility delivery. CY program participation is defined as a below poverty line (BPL) or tribal mother who delivers in a CY approved facility. Program non participation is defined as BPL or tribal mother who delivers outside of a CY approved facility.

Stratified systematic random sample will be used to select the study villages in each district. The districts will first be stratified by blocks (administrative units) and then the villages in each block will be classified into two strata based on the size of the population. Villages will be randomly selected from each strata based on the population proportion. Given the different design of each program, the sample sizes will vary in each province.

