There will be three points of data collection; (i) when the woman delivers, (ii) 15 days and (iii) 28 days post-delivery. The ASHA will administer a simple symptom based checklist to all mothers regardless of place of delivery to ascertain maternal morbidity, complications associated with the pregnancy and delivery, at the three time points. To ensure quality data collection, a physician will administer a second checklist to 5% of all mothers which will be compared to the data collected by the ASHA.

Socio-demographic details, history of previous pregnancies, receipt of comprehensive maternal health care (antenatal, intrapartum and post natal care), place of delivery, delivery type, birth weight, immunization of the child, indirect and direct costs associated with delivery, program participation and maternal and neonatal outcomes will be elicited post-delivery in the mother’s home by a trained research assistant. In addition, reasons for participation/non-participation in the program, reasons for their choice of facility and barriers (if any) to access of care will be collected. Data will also be collected on household amenities and assets. This will help create an indicator to assist in quantifying the degree of income related inequalities and how it influences the inequities in access to care. In the event of a maternal death, the head of the household will be requested to provide the information.

Propensity score matching will be used to select a comparison group from the sample of non-participants closest in terms of observable characteristics to a sample of program participants. Comparisons of the outcome variables described above between the two groups (users and non-users) will be studied. Reasons for participation/non participation will be described. In a separate hierarchical model, the predictors of non-participation will be studied in each program. Costs incurred will be compared by place of delivery.

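### Participation is defined by place of birth, so if home births are weighed less often or recalled less accurately, the matched user versus non-user comparison of birth weight is distorted in a way matching cannot correct

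*Protocol article*

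**What the plan says.** In the Protocol article, the Background section, objective vii, lists the items to be compared between beneficiaries and eligible non-beneficiaries in the community. They include "delivery outcome, birth weight, receipt of post natal care, immunization of the child and costs of care incurred".

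The community-level part of Data collection methods gives the sample as "women residing in the selected study villages who delivered in the last year". Birth weight stands in the list "place of delivery, delivery type, birth weight, immunization of the child, indirect and direct costs associated with delivery", and these items "will be elicited post-delivery in the mother’s home by a trained research assistant". The same part says that non-participants will be matched to participants by propensity score on observable characteristics, and that the listed outcomes will then be compared between users and non-users. The Discussion names this contrast as the second assessment of impact.

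The exposure definitions are:
- JSY. For the participant arm the article states: "JSY program participation is defined as an institutional delivery in any public health facility". For the comparison arm it states: "Program non participation is defined as a home or private facility delivery".
- CY. For the participant arm the rule reads: "CY program participation is defined as a below poverty line (BPL) or tribal mother who delivers in a CY approved facility". For the remaining eligible mothers it reads: "Program non participation is defined as BPL or tribal mother who delivers outside of a CY approved facility".

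The one contact described for all mothers at the time of birth is a symptom checklist on maternal morbidity and complications, administered by the ASHA. The article does not mention weighing there.

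**The concern.** A birth weight reported at interview is only as good as the weighing behind it. Whether a baby was weighed, and whether the figure was written down, plausibly depends on where it was born. In this design place of birth is the exposure. Any such dependence therefore appears as a difference between the two arms in how complete and how accurate the weights are.

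Propensity matching makes the mothers in the two arms alike in background. It does not make their babies equally likely to have been weighed, because two mothers with the same score can still differ in place of delivery, and in a matched pair they do. If unweighed births drop out, the weights left among non-participants over-represent facility births. If they are filled in by recall, measured values in one arm are set against a mixture in the other. In either case the difference in birth weight would carry a component that is not an effect of the program, within a contrast that the article labels as impact.

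**Working it through.** The article states no birth-weight effect, standard deviation or sample size, so there is no figure of its own to reproduce. The check asks what share of non-participants would have a weight.

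**Inputs from the article**
- Institutional delivery is 47% in Madhya Pradesh and 56% in Gujarat (Table 3; province level).
- The JSY and CY definitions are those quoted above.

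**Assumptions, not in the article**
- x = private births as a percentage of all births in Madhya Pradesh, 5 to 20.
- h = share of home births weighed, 0 or 20% in the main calculation.
- All facility births are weighed (95% in one variation).
- c = CY births as a percentage of births in Gujarat, 10 to 40.

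**JSY**

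Home births = 100 − 47 = 53% of births. Non-participants = 53 + x. Share of non-participants with a weight = (x + 53h)/(53 + x).

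| x | h = 0 | h = 20% |
|---|---|---|
| 5 | 5/58 = 8.6% | (5 + 10.6)/58 = 26.9% |
| 10 | 10/63 = 15.9% | (10 + 10.6)/63 = 32.7% |
| 20 | 20/73 = 27.4% | (20 + 10.6)/73 = 41.9% |

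Under the same assumption every participant has a weight.

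**Sensitivity to h**

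Let 20% of non-participants be facility births and let 95% of facility births be weighed. Availability among non-participants is 0.20 × 0.95 + 0.80h.

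| h | Non-participants with a weight | Facility births among those weighed |
|---|---|---|
| 0 | 19% | 100% |
| 10% | 27% | 70% |
| 30% | 43% | 44% |
| 95% | 95% | 20% |

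In the last row availability equals that of participants, and the facility share among the weighed equals the true share. There is then no distortion from missing weights.

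**Sensitivity to the institutional rate**

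If 80% of births were institutional and 30% of those private, private births would be 24% of all births and non-participants 20 + 24 = 44%. Private births would then be 24/44 = 55% of non-participants, so availability would be at least 55%, given that all facility births are weighed.

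**CY**

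Non-participants include public and non-approved private facility births as well as home births. Facility share of non-participants = (56 − c)/(100 − c).

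| c | Facility share | Home share |
|---|---|---|
| 10 | 46/90 = 51% | 49% |
| 20 | 36/80 = 45% | 55% |
| 30 | 26/70 = 37% | 63% |
| 40 | 16/60 = 27% | 73% |

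The 56% covers all mothers, not only those below the poverty line or tribal, so these figures are indicative.

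**The case against.** The strongest reply is that the premise is external. The article nowhere says that home births go unweighed or that facility births are always weighed. It describes one task of the ASHA at the birth contact and does not claim to list all of them. The questionnaire is not shown and may already ask for the source and date of the weight, and rules for missing values may sit in the full protocol or analysis plan. If home births are weighed as often as facility births, the missing-data problem disappears. The 47% is a province-wide figure applied to villages in three purposively chosen districts, after seven years of program operation. The private share of 5 to 20% is assumed.

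Most of this stands as a limit on the size of the problem. It also rules out some stronger readings that a reader might reach:
- That the comparison is in effect public against private facilities. This needs almost no home births to be weighed and fits JSY only. CY non-participants may also deliver in public facilities, and facility births need not be a minority among them.
- That the missing weights all lie in one arm. The article gives no figure for weighing in any setting.
- That the program would look harmful for birth weight because private-facility users are better off. The article does not show this, and matching on socio-demographic characteristics is aimed at that very difference.
- That silence on the source of the weight is an error in itself. In a condensed article it is not.

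The reply does not touch the structure. The article itself fixes the exposure as place of birth, collection at a home interview, and a user versus non-user comparison read as impact. A later missing-data rule cannot recover a weight that was never taken, or a source that was never asked about.

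**Conclusion.** The concern holds conditionally. The article fixes an exposure that coincides with place of birth and commits to comparing an outcome whose availability and accuracy may depend on place of birth. If they do, the bias is tied to the exposure and background matching cannot remove it.

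For JSY, with institutional delivery at 47%, private births at 5 to 20% of all births and every facility birth weighed, 9 to 27% of non-participants would have a weight when no home birth is weighed, and 27 to 42% when a fifth are. The gap narrows as home weighing rises or as institutional delivery exceeds 47%. For CY the mechanism is the same, but the mix of non-participants differs and the JSY figures should not be carried over.

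Error in recalled weights is as possible as missing weights, and the interview may take place up to a year after the birth. The documents support no statement on the direction or size of the resulting difference in birth weight. The point affects one of several outcomes and should be settled before fieldwork.

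**What to change.** 1. At the home interview, record whether the baby was weighed, when, and whether the value was read from a card or recalled.
2. In each program, report the proportion of births with a weight, and its source, by place of delivery: home, public facility, private facility and, for Gujarat, CY-approved facility.
3. Base the birth-weight comparison on recorded weights and show it by place of delivery, so that the reader sees which births are being compared. Restricting to recorded weights is itself a selection, which is why the breakdown is needed.
4. State in advance that the overall user versus non-user difference in birth weight will not be interpreted as program impact unless availability is similar across places of delivery.

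The cost is a few questionnaire items, if they are not already there, and a narrower claim for this outcome. Where few home births have a recorded weight, little can be said about birth weight among them.
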